### Procedures

#### Baseline assessments

Consenting healthcare professionals will receive information about the study. During a 2-month study period, baseline measurements will be performed.

The quasi-experimental design is based on pre- and post-measurements to assess the proportion of patients asked about possible exposure to IPV and identify persons exposed to IPV. Baseline measurement will be recorded (before randomisation to intervention) by all participating clinics over a 2-month period regarding how many patients they identify who have been exposed to IPV.

In terms of the *health clinics* and *youth guidance clinics*, data regarding the number of patients asked about IPV and the number of patients exposed to IPV will be retrieved from the medical record system Take Care, in which healthcare professionals document whether they have asked the patient about exposure to violence and what the patient has responded. This will be carried out by healthcare professionals as part of their regular documentation of the patient’s medical visit. Information about measures taken and the support given by the healthcare professional if the patient reports exposure will also be documented and retrieved from the same medical system.

Notably, in relation to *maternity clinics*, there are no diagnostic codes for exposure to IPV, and this information cannot thus be searched for in patients’ medical records. The research group has therefore developed a simple protocol in which healthcare professionals can record statistics on how many patients have been asked about possible exposure to IPV and how many patients have disclosed exposure to IPV during the study period.

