#### Allocation of intervention

Health clinics, youth guidance clinics and maternity clinics will have separate allocations divided equally between the three interventions, together with a matching of socioeconomic status of the area where the clinic is located and the number of participants at the clinic (healthcare professionals). The allocation of healthcare units will be determined to avoid contamination between the three interventions, while the inclusion of socioeconomic status and the number of participants aims to balance the interventions. The healthcare units will be allocated separately by randomisation to intervention 1, 2 or 3.

The CNI will be used as a measure of socioeconomic status and is an instrument that is used to identify health risks at the area level using factors such as elderly people living alone, children below the age of 5, unemployment, low education, lone parents, relocation and migrants.^28^ The CNI will be coded as high or low, and the number of participants will be coded as two groups: many (>X?) or few (<X?). Computerised randomisation will be carried out using SPSS (version 29.0) during baseline. The clinics will be informed after baseline assessments.

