### Data analysis and statistics

#### Quantitative analysis

Data will be analysed at group level within each study setting (health centres, maternal health clinics and youth guidance centres). The analysis will primarily involve pre- (baseline) and post-intervention assessments, comparing the number of patients asked about IPV and identified of IPV exposure during baseline and after the intervention period using logistic regression analyses (with patients asked about IPV and patients identified with IPV exposure as outcomes and time (pre and post) and intervention arms and a time×intervention interaction term as predictors. Covariates will be used when relevant.

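### The time×intervention contrast estimates a separate baseline for each arm although units are randomised; it is valid, but less precise than a shared-baseline mixed model of the same data

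*Protocol article*

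**What the plan says.** Three parts of the protocol article bear on this.

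- *Allocation of intervention.* "The healthcare units will be allocated separately by randomisation to intervention 1, 2 or 3". Each type of clinic has "separate allocations divided equally between the three interventions", with matching on area socioeconomic status and number of participating professionals. On timing: "Computerised randomisation will be carried out using SPSS (version 29.0) during baseline. The clinics will be informed after baseline assessments".
- *Baseline assessments.* "Baseline measurement will be recorded (before randomisation to intervention) by all participating clinics over a 2-month period".
- *Quantitative analysis.* "Data will be analysed at group level within each study setting". The model is a logistic regression for patients asked and patients identified, with time (pre and post), "intervention arms and a time×intervention interaction term as predictors". On adjustment it adds only: "Covariates will be used when relevant".

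The Recruitment section gives 6 health centres, 10 maternal health clinics and 11 youth guidance clinics, 27 units in all.

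**The concern.** In a model with time, arm and time×arm, the arm main effect lets each arm have its own baseline level, and the arms are compared through the interaction. That is the natural contrast when arms may differ systematically before treatment. Here they cannot. The article places randomisation after baseline in one section and during baseline in another, but on either reading clinics do not know their arm while baseline is recorded. The label quasi-experimental does not alter this.

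The interaction therefore subtracts the whole of a chance baseline difference between arms, although only part of it is expected to persist into the post period. With 27 units in three arms, about nine per arm, the number of units limits precision. There is also no untreated arm, so the between-arm contrast is the only comparison that randomisation protects.

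**Working it through.** **The plan's own figures.** The sample size paragraph gives 6000 × 0.07 = 420 cases per arm, which reproduces. It states no precision for an arm contrast and no pre/post correlation, so there is no planned figure to test. r is an assumption throughout.

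**Large-sample formula.** Take unit-level outcomes with equal variance σ² before and after, correlation r, and n units per arm.

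- Difference in changes: variance = 2σ²(1 − r) × 2/n.
- Using a shared or adjusted baseline: variance = σ²(1 − r²) × 2/n.
- Ratio = (1 − r²) / [2(1 − r)] = (1 + r)/2.

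This gives 0.65 at r = 0.3, 0.75 at r = 0.5, 0.90 at r = 0.8 and 0.95 at r = 0.9. With unequal standard deviations σ0 (pre) and σ1 (post), the excess variance of the change contrast is proportional to (σ0 − rσ1)², which is never negative.

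**Plausible r (all inputs assumed).** 6000 patients per arm over nine units is 667 per unit, or 333 if the total covers both periods. With intracluster correlation (ICC) 0.01 to 0.10 and between-period autocorrelation (CAC) 0.5 to 0.9, r = CAC × ICC × m / [1 + (m − 1) × ICC].

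- Lowest: 0.5 × 3.33 / 4.32 = 0.39.
- Highest: 0.9 × 66.7 / 67.6 = 0.89.

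**Small-sample check of a shared-baseline model.** Unit-level normal data were simulated with arm sizes taken as 2/2/2, 3/3/4 and 4/4/3. The model had a common baseline within setting, setting×time, arm effects in the post period only, and a pre/post correlation estimated by REML and kept at zero or above. The entries are variance relative to the interaction. The pooled column shows the range of two separate simulations.

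| r | 27 pooled | 6 health centres | 10 maternal | 11 youth |
|---|---|---|---|---|
| 0.3 | 0.66–0.67 | 0.76 | 0.70 | 0.70 |
| 0.5 | 0.75–0.77 | 0.89 | 0.82 | 0.80 |
| 0.8 | 0.92 | 1.02 | 0.96 | 0.95 |
| 0.9 | 0.97–0.98 | 1.03 | 0.96 | 0.97 |

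For the pooled analysis, the square roots give standard errors smaller by about 18%, 12 to 13%, 4% and 1 to 1.5%.

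**Two fixes that do not work.**

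1. *Separate unit-level covariance analyses (ANCOVA) within settings.* Estimating the baseline slope from few units multiplies the variance on average by 1 + 1/(f − 2), where f is the residual degrees of freedom before the slope is added. The ratio to the interaction becomes [(1 + r)/2] × [1 + 1/(f − 2)].
   - 6 units, f = 3: ratio = 1 + r, or 1.30, 1.50 and 1.80 at r = 0.3, 0.5 and 0.8. Simulation gave about 1.15 to 1.9. Residual degrees of freedom fall from 3 to 2, and the 95% t value rises from 3.18 to 4.30.
   - 10 units, f = 7: ratio = 0.60(1 + r), above 1 from r = 0.67.
   - 11 units, f = 8: ratio = 0.583(1 + r), above 1 from r = 0.71.
2. *Deleting the arm term with no unit effect.* The arm contrast then becomes a post-only comparison with variance σ² × 2/n. This exceeds 2σ²(1 − r) × 2/n whenever r > 0.5.

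**The case against.** The strongest reply is that nothing here is wrong in the sense of bias. The interaction is a valid contrast under randomisation. The Outcome measures section says the analyses will mainly be pre/post comparisons, and those are untouched. The same units are measured in two 2-month periods, so r may well be 0.8 or more, where the gain is a few per cent. A condensed article may also leave covariate detail to an analysis plan that is not shown.

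Most of this stands and limits the point to efficiency. It does not remove it. Study design and the sample size paragraph both make comparison of the interventions a purpose, and the article fixes the model terms instead of leaving them open. The sentence on covariates does not supply a shared baseline, because baseline is already an outcome row in the stated model.

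A reader might also infer that every arm contrast will have wider intervals than necessary, or that at r = 0.5 the choice amounts to having 27/0.75 = 36 units instead of 27. The article does not support either. It analyses within each setting, where the large-sample ratio does not carry over to 6, 10 or 11 units, and it gives no r. Nor can covariate adjustment and the shared-baseline model be treated as interchangeable here: they agree only in large samples, and with six units they point in opposite directions at r of 0.3 and 0.5.

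**Conclusion.** The point holds as a loss of precision in the between-arm contrast. Units are randomised, baseline is measured before clinics know their arm, and the stated model still estimates a separate baseline per arm. Pooled over 27 units, a shared-baseline model cuts the variance by about a third at r = 0.3, a quarter at r = 0.5, 8% at r = 0.8 and 2 to 3% at r = 0.9. Within the six health centres the two approaches roughly tie at r of 0.8 or more.

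These sizes rest on an assumed r, near-normal unit-level outcomes with equal variances and equal weights, and arm sizes as even as 6, 10 and 11 units allow. The reading that the planned analysis is biased or invalid is not supported, and within-arm pre/post comparisons lie outside the point.

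**What to change.** Replace the primary between-arm contrast with a pre/post mixed logistic model that has:

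- a unit random effect for each period, correlated across periods;
- a baseline mean common to the three arms within setting;
- arm effects in the post period only;
- preferably all 27 units pooled, with setting and setting×time as factors.

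Keep the time×arm model as a sensitivity analysis. Do not substitute separate unit-level baseline-covariate models within settings, and do not merely drop the arm term from a model without a unit effect. The change should be fixed before results by arm are seen.

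The cost is a few sentences of analysis text, somewhat more modelling work, and reliance on a mixed model with few units. No new data are needed.

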### Qualitative data

In addition to the quasi-experimental design, the study includes a qualitative component aimed at exploring healthcare professionals’ experiences of the interventions. This part of the study is based on a qualitative interpretative design using thematic analysis.^30^ Focus group interviews^31^ will be conducted with participants from each care unit type (primary health centres, maternal health clinics and youth guidance clinics), representing all three intervention arms. The interviews will be transcribed verbatim and analysed inductively to identify patterns and themes related to perceived effectiveness, feasibility and clinical relevance of the interventions. This qualitative approach is intended to complement the quantitative findings and provide a deeper understanding of the interventions’ impact in clinical practice.

### Ethics and dissemination

The project has received ethical approval (Dnr 2023-03399-01) and complies with the Declaration of Helsinki. Ethical considerations include potential triggers for health professionals who have experienced violence themselves. In the event of such an incident, a psychologist or psychotherapist research team member with IPV competence will provide support and guidance. Further, sensitive situations may arise if attitudes about people exposed to IPV are discussed in focus groups. Considering this, study participation is voluntary and can be discontinued at any time. One ethical question concerns what the additional value of the study is for individuals exposed to IPV. We believe that the study will contribute new knowledge about how health professionals can ask, identify and respond to IPV exposure to these patients and thus, in the longer term, we believe this project can contribute to an increased ability to offer support to individuals exposed to IPV. The project is likely to result in an increase in the number of individuals asked about IPV when visiting primary care. Previous research indicates that both victims and non-victims appreciate being asked about violence by healthcare professionals. Screening for IPV in this study is conducted within healthcare units that have established local protocols for responding to disclosures of violence. Prior to inclusion, all participating units confirmed access to resources and referral pathways for appropriate support. Ethical approval was granted on the basis that these safeguards are in place, ensuring that screening does not occur in isolation but as part of a structured response system.

The results will be disseminated to the scientific community through articles and at conferences. Clinical healthcare professionals will be educated about the study results, and student curricula will be updated. The results will be disseminated to society via social media, magazines and newspapers.
